### Participant patients

Participants’ inclusion criteria are as follows:
At the age of 18 to 80;Diagnosed as sepsis (a possible or specific proof for infection plus Sequential Organs Failure Assessment (SOFA) scores ≥ 2) [21].

Participants’ exclusion criteria are as follows:
Patients once having received RRT;Patients requiring RRT prior to enrolment;Patients possessed with only one kidney;Patients with a medical history of renal transplant;AKI caused by permanent kidney artery embolism or surgery injury to kidney artery;AKI caused by glomerulonephritis, interstitial nephritis, or vasculitis;AKI caused by postrenal obstruction;Hemolytic uremic syndrome (HUS) or thrombotic thrombocytopenic purpura;Patients having received fluid resuscitation over 1000 ml within 6 h prior to ICU;Patients with serum chloride more than 120 mmol/l;Pregnant women; andPatients enrolled into another clinical trial at the same time.

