### Parallel control and allocation

Patients will be divided into 2 parallel groups: acetate Ringer’s solution versus saline. Crystalloids for enrolled patients are assigned according to the number of the month. Once assigned, the solution will be applied for the first 5 days during the patients’ stay in ICU. The assignment remains during change of month. The solution applied in the beginning month in each ICU is determined randomly by Excel2016 of Microsoft Office to make sure that stratified patient groups will be randomized to receive either acetate Ringer’s or saline solution, followed by a monthly rotation of fluids, so that any potentially observed difference in renal function is not due to other confounding factors such as use of nephrotoxic medication or contrast media. According to the Excel2016-generated random numbers, acetate Ringer’s solution will be applied in the odd month and saline will be applied in the even month both in the 2 centers. The random number table is operated by the primary investigator alone and clinicians are not involved in the process.

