### Study outcomes

The primary outcome is MAKE28 (major adverse kidney events) [22]—a composite of in-hospital death, new renal replacement therapy, or persistent renal dysfunction (defined by an estimate glomerular filtration rate (eGFR) lower than 60 ml/min/1.73 m^2^ for at least 3 months [23, 24]) within 28 observational days.

Secondary outcomes will include:
The occurance of AKI which is diagnosed according to the Kidney Disease Improving Global Outcomes (KDIGO) criteria [25];Twenty-eight day mortality;Electrolyte disturbance, including hypernatremia, hyperchloremia, and hyperkalemia as well as hyponatremia, hypochloremia, and hypokalemia;Changes of renal functions based on the biomarkers measured from the participants’ plasma and urine samples collected in the first 3 days after enrolment; andOther clinical outcomes: ICU stay days, ventilator days, vasopressor days, and RRT days.

Pre-specified subgroups for primary and secondary outcome analyses will mainly include:
With or without acute kidney injury (no AKI, AKI stage 1, AKI stage 2, or AKI stage 3);With or without septic shock;Low versus high severity of sepsis: mild, moderate, and severe (classified by SOFA scores or Acute Physiology and Chronic Health Evaluation II (APACHE II) scores); andIntravenous infused volumes of the assigned crystalloids.

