### Statistical analysis

Measurement data that conform to normal distribution will be described as mean ± SD, while ones that do not will be reported as the median and interquartile range (IQR). Count data will be notified as frequencies and proportions. As for single-factor analysis, the difference of measurement data will be compared with *T* test between two groups or with one-way analysis of variance among three groups. Chi-square test and Fisher’s exact test will be used for rate comparison. As for multi-factor analysis, variables which showed a significant difference in the univariate analysis will be processed by logistic multivariate regression analysis. Multiple linear regression analysis will be used to demonstrate the linear relationship between variables. *P* value < 0.05 will be considered statistically significant. SPSS 24.0 will be used to complete data processing and statistical analysis.

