### Primary analysis

The primary analysis will be an intention-to-treat comparison of the primary outcome of MAKE28 between the saline and acetate Ringer’s solution. A generalized linear mixed-effects model will be used including fixed effects (sex, age, body mass index, group assignment, principal diagnosis, crystalloids received prior to ICU, SOFA score, APACHE II score, mechanical ventilation status, vasopressor usage, etc.) and random effects. It is aimed to describe patients’ baseline characteristics and eliminate confounding factors.

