### Additional secondary analysis

Statistical methods mentioned in the statistical analysis will be applied according to the characteristics and distribution of the data.
Compare the secondary outcome between the two groups;Subgroup analysis will include:
Septic shock (yes/no)Stage of AKI on the enrolment day (no AKI, AKI, chronic kidney disease without receiving RRT regularly)intravenous volumes of the assigned crystalloidsThe APACHE II scores and SOFA scores at the day of enrolmentReceipt of mechanical ventilation (yes/no) and ventilation daysReceipt of vasopressor (yes/no), vasopressor category, and max dosesReceipt of RRT (yes/no) and RRT daysMain diagnosis at the time of admission to hospital (nervou s system disease, respiratory system disease, cardiovascular system disease, digestive system disease, urinary system disease, hematologic system disease, endocrine system disease)Complications (hypertension, diabetes, coronary heart disease, etc.)

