### Data collection and management

Patients’ demographic data, main diagnosis, comorbidities, assigned crystalloids, general vital signs, SOFA scores, APACHE II, infection indices, and indices of multi-organ function including renal function, respiratory function, cardiac function, etc. at the time of enrolment will be collected as baseline data. Clinical information including infection indices (white blood cell count, procalcitonin, etc.), organ function indices (renal function (creatinine, urea nitrogen, cystatin C, urine volumes, etc.), respiratory function (PO_2_/FiO_2_, ventilation situation, etc.), hepatic function (total bilirubin, etc.), and indices of internal environment (blood gas analysis) will be detected during the first 5 days in ICU, and treatments such as vasopressors, mechanical ventilation, RRT, and electrolyte supplement will be recorded. These data and infused volumes of the assigned fluids will be collected for at least 5 days or until ICU discharge. ICU stay days, vasopressor days, RRT days, and ventilation days will be counted during 28 days after enrolment. These data will be collected to assess and analyze primary and secondary outcomes. Besides, patients’ blood and urine samples within the first 3 days after enrolment will be collected and stored for testing possible biomarkers for identifying AKI at an early stage.

Patients’ information and clinical data will be collected from the Hospital Information System (HIS) of the hospitals involved in this study and recorded in the Case Report Format (CRF) by the trial manager or trained personnel. An electronic password-protected excel, which will be applied for statistical analysis, will be created to summarize the data of all participants. All the data will be accessed by only investigators and authorized personnel to monitor the completeness and authenticity of the table. The confidentiality is secured and all the data will be preserved for the purpose of a secondary analysis or investigations by the investigators. To protect patients’ privacy, their names will not appear on the CRF table. Every participant will only be recognized by their study ID.

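### Electrolyte disturbance is not limited to new or worsened cases, and no planned analysis is sure to use the enrolment value, so the contrast between fluids may be diluted (minor, secondary outcome)

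*Protocol article*

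**What the plan says.** **Outcome.** Study outcomes lists "Electrolyte disturbance, including hypernatremia, hyperchloremia, and hyperkalemia as well as hyponatremia, hypochloremia, and hypokalemia". It ties none of the six conditions to the patient's state at enrolment. The same section counts renal replacement therapy in the primary outcome only when it is new.

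**Entry.** Under Participant patients, the one electrolyte exclusion is "Patients with serum chloride more than 120 mmol/l". Sodium, potassium and low chloride carry no limit. Fluid resuscitation of up to 1000 ml in the 6 hours before ICU does not exclude a patient.

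**Analysis.** For secondary outcomes, Additional secondary analysis refers back to the general methods: "Statistical methods mentioned in the statistical analysis will be applied according to the characteristics and distribution of the data". In Statistical analysis these are "Chi-square test and Fisher’s exact test will be used for rate comparison", followed by a multivariable step in which "variables which showed a significant difference in the univariate analysis will be processed by logistic multivariate regression analysis". The same section also lists t tests and linear regression for measured quantities. The one adjusted model with named covariates, in Primary analysis ("A generalized linear mixed-effects model will be used including fixed effects"), is for MAKE28. Its list is open-ended but names no electrolyte.

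**Data.** Data collection and management states that "indices of internal environment (blood gas analysis) will be detected during the first 5 days in ICU".

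**Allocation.** Parallel control and allocation states that "acetate Ringer’s solution will be applied in the odd month and saline will be applied in the even month both in the 2 centers". Study fluid distribution and logistics confirms that the trial is open label.

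**The concern.** Chloride load is the mechanism that the article puts forward (Background and rationale; Summary/discussion). The two fluids contain 154 and 115 mmol/L of chloride (Table 2), so electrolyte disturbance is the outcome closest to that mechanism.

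A patient who is already hyperchloraemic at enrolment says little, through a yes/no count, about what the study fluid did. If such patients count as events, they add the same block of events to both arms and make the fluids look more alike than they are. The enrolment value would separate the two situations, but nothing in the stated methods ensures that it is used. The logistic step admits a variable only if it happens to be significant in a univariate test.

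Allocation adds a second issue. Staff know which fluid an enrolling patient will receive, so the arms could differ in electrolytes at entry by more than chance. An unadjusted rate comparison would carry that difference into the result.

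**Working it through.** The plan gives no rate, effect size or power for electrolyte disturbance, so there is no figure to reproduce. The calculation below shows the size of the effect under assumed rates.

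**Inputs**
- From the article: 156 patients per arm (Sample size and statistical power); significance at P < 0.05 (Statistical analysis), taken here as two-sided.
- Assumed: new-onset rates p of 40% (saline) and 25% (acetate Ringer's) in patients undisturbed at entry; share b disturbed at entry from 0 to 40%; every patient disturbed at entry counts as an event.

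**Step 1: equal prevalence in both arms.** The crude rate is b + (1 − b)p. The crude difference is therefore (1 − b)(p_S − p_A).

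At b = 0.20:
- Saline: 0.20 + 0.80 × 0.40 = 0.52.
- Acetate Ringer's: 0.20 + 0.80 × 0.25 = 0.40.
- Difference: 12 points, which is 0.80 × 15.

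Power is Φ[(d − 1.96·SE0)/SE1]. SE0 comes from the pooled rate and SE1 from the separate rates. At b = 0.20 and n = 156:
- SE0 = √(2 × 0.46 × 0.54/156) = 0.0564.
- SE1 = √((0.52 × 0.48 + 0.40 × 0.60)/156) = 0.0560.
- Power = Φ[(0.12 − 0.1106)/0.0560] = 0.57.

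The last column restricts the analysis to patients undisturbed at entry, with 156(1 − b) per arm.

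| b | Crude saline | Crude Ringer's | Difference (points) | Power, crude | Power, undisturbed at entry only |
|---|---|---|---|---|---|
| 0% | 40.0% | 25.0% | 15.0 | 0.81 | 0.81 |
| 10% | 46.0% | 32.5% | 13.5 | 0.69 | 0.77 |
| 20% | 52.0% | 40.0% | 12.0 | 0.57 | 0.72 |
| 30% | 58.0% | 47.5% | 10.5 | 0.46 | 0.66 |
| 40% | 64.0% | 55.0% | 9.0 | 0.37 | 0.59 |

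**Step 2: equal prevalence, no fluid effect.** With p_S = p_A the crude difference is (1 − b) × 0 = 0, and the rejection rate stays at 5%.

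**Step 3: unequal prevalence, no fluid effect.** With a common new-onset rate p, the spurious difference is (b_S − b_A)(1 − p). For p = 30% (assumed):
- 25% v 20% at entry: 0.05 × 0.70 = 3.5 points; rejection probability about 10%.
- 30% v 20%: 7.0 points; about 24%.
- 35% v 20%: 10.5 points; about 46%.

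Imbalance can also hide a real effect. With new onset of 40% v 25% and entry prevalence of 15% (saline) v 25% (Ringer's), the crude rates are 0.15 + 0.85 × 0.40 = 49.0% and 0.25 + 0.75 × 0.25 = 43.75%. A 15-point effect then shows as 5.25 points.

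**Step 4: how much imbalance is ordinary.** Under individual randomization the chance SD of the entry difference is √(2b(1 − b)/156). This is 3.4 points at b = 10% and 5.5 points at b = 40%. The 5% test already allows for variation of that kind. It does not allow for systematic differences arising from a known monthly schedule.

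**The case against.** **The article does not say that prevalent cases are counted.** This stands. It says neither that they are counted nor that they are left out. Thresholds, time windows and onset rules commonly sit in a full protocol or analysis plan that is not shown, and their absence here is no error. The dilution is therefore conditional on how the outcome is finally coded.

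**The analysis is not only a crude test.** This also stands in part. Regression methods are listed, and nothing rules out analysing chloride as a measured quantity. However, selecting covariates by univariate significance does not guarantee that the enrolment value enters, and the only model with named covariates is for MAKE28.

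**A reader might infer that disturbance present at entry will be read as an effect of the study fluid.** The documents do not support this. Prevalent cases fall in both arms; when the shares are equal they weaken a true contrast and produce no false one (Step 2). A false effect needs unequal prevalence. The allocation scheme makes that possible, but nothing in the article shows that it occurs.

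**A reader might also credit baseline adjustment with a large saving in sample size.** With assumed correlations of 0.4 to 0.7, the variance factor 1 − r² is 0.84 to 0.51, equivalent to 1.19 to 1.96 times as many patients. That compares an adjusted with an unadjusted continuous analysis. It does not measure what is lost by the binary test for rates, so it is not used here.

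**Conclusion.** The point holds in a limited form. Patients may enter with abnormal sodium, potassium or chloride, the outcome is not confined to new or worsened disturbance, and use of the enrolment value is not assured. If prevalent cases are counted, the difference between fluids shrinks by the factor (1 − b): from 15 to 12 points, with power falling from 0.81 to 0.57, at an assumed b of 20% and assumed new-onset rates of 40% and 25%. Bias in either direction needs unequal prevalence at entry, which predictable open-label allocation makes possible but which is not demonstrated. All prevalences and event rates are assumptions, because the article gives none. This is a minor point on one secondary outcome with no stated power, and it does not touch the primary analysis.

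**What to change.** 1. Analyse chloride, sodium and potassium over days 1–5 as continuous outcomes adjusted for the enrolment value, by ANCOVA or a repeated-measures model. Fix the enrolment value as a covariate in advance instead of leaving it to univariate selection.
2. Report the six disturbance rates as new or worsened since enrolment, with worsening defined, or adjust them for the enrolment value.

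Restricting the comparison to patients normal at entry should not be the main remedy. At b = 20% it leaves about 125 of 156 per arm (156 × 0.80 = 124.8), and it ignores worsening in the others. Its power in the illustration is 0.72: better than the crude 0.57, but bought by discarding patients. Adjustment deals with imbalance in the measured electrolyte only and does not cure other selection that the monthly allocation might allow.

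**Cost:** slightly more analysis work, specified before results are seen. Chloride must be known at entry to apply the exclusion, and internal-environment indices are collected over the first 5 ICU days. The article does not name sodium or potassium among the baseline data and gives no sampling frequency, so the trial team should confirm that the case report form records enrolment sodium and potassium, and how often all three are measured.

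### As printed, the electrolyte-disturbance outcome is not limited to disturbances arising after enrolment, and its rates are compared without adjustment for enrolment values

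*Protocol article*

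**What the plan says.** Under Study outcomes, the protocol article gives one of the secondary outcomes as "Electrolyte disturbance, including hypernatremia, hyperchloremia, and hyperkalemia as well as hyponatremia, hypochloremia, and hypokalemia". Table 1 repeats the list. Neither place gives cut-offs, a time window or a rule for disturbances present at enrolment. In the same section the primary outcome is "a composite of in-hospital death, new renal replacement therapy, or persistent renal dysfunction", so the restriction to new events is written for renal replacement therapy but not for electrolytes.

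Under Participant patients, the only electrolyte criterion is the exclusion of "Patients with serum chloride more than 120 mmol/l". There is no lower limit for chloride and no limit for sodium or potassium.

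Under Data collection and management, "indices of internal environment (blood gas analysis) will be detected during the first 5 days in ICU". The section does not say whether the first of these values counts as baseline or as outcome.

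For the analysis, Additional secondary analysis says "Compare the secondary outcome between the two groups" and refers back to the general methods. Under Statistical analysis those state "Chi-square test and Fisher’s exact test will be used for rate comparison", with a significance level of 0.05. No adjustment for an enrolment electrolyte value is named.

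Under Parallel control and allocation, acetate Ringer's solution is used in odd months and saline in even months at both centres. The trial is open label.

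**The concern.** A patient who is already hyponatremic, hypokalemic or hyperchloremic at enrolment did not become so because of the study fluid. If such patients count as events, they add the same amount to both arms and pull the comparison towards no difference. If they are more common in one arm, the excess appears as a fluid effect.

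This matters most for chloride. The Background and the Summary/discussion put forward the chloride load of saline as the route to kidney harm, and Table 2 gives 154 mmol/L for saline against 115 mmol/L for acetate Ringer's solution. The electrolyte outcome is where that mechanism would show. Because the fluid for the month is known before a patient is enrolled, balance at entry is less secure than under concealed individual randomisation, and the stated rate test does nothing to correct an imbalance.

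**Working it through.** The article states no rate, power or sample size for this outcome, so there is no figure to reproduce. The check is of direction and of possible size.

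**Inputs from the article:** 156 patients per arm and a 20% withdrawal allowance (Sample size and statistical power); significance level 0.05, taken here as two-sided (Statistical analysis).

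**Assumed inputs, not in the article:** new-onset hyperchloremia in 40% of unaffected patients on saline and 25% on acetate Ringer's solution; a share b already affected at enrolment, equal in both arms, from 10% to 30%; every prevalent case counted as an event.

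**Step 1, dilution.** With new-onset risk p among unaffected patients, the counted rate in an arm is b + (1 - b)p. The difference between arms is (1 - b)(p_saline - p_acetate). It shrinks by the factor (1 - b) for any b above zero.

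**Step 2, power.** Power = Φ[(d - 1.96·SE0)/SE1], where d is the rate difference, SE0 the pooled and SE1 the unpooled standard error.

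At b = 20%, counting prevalent cases:
- rates 0.20 + 0.80 × 0.40 = 52% and 0.20 + 0.80 × 0.25 = 40%, so d = 12 points
- SE0 = √(2 × 0.46 × 0.54/156) = 0.0564; SE1 = √((0.52 × 0.48 + 0.40 × 0.60)/156) = 0.0560
- (0.12 - 1.96 × 0.0564)/0.0560 ≈ 0.17, so power is about 57%

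At b = 20%, new onset only:
- 156 × 0.80 ≈ 125 per arm, 40% versus 25%, d = 15 points
- SE0 = 0.0593; SE1 = 0.0585
- (0.15 - 1.96 × 0.0593)/0.0585 ≈ 0.58, so power is about 72%

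| b | Difference if prevalent cases count | Power if they count (156 per arm) | Power, new onset only (156(1 - b) per arm) |
|---|---|---|---|
| 10% | 13.5 points | 69% | 77% |
| 20% | 12.0 points | 57% | 72% |
| 30% | 10.5 points | 46% | 66% |

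With no prevalent cases (b = 0) the difference is 15 points and power is about 81%.

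**Step 3, withdrawal.** With 156 × 0.80 ≈ 125 per arm, the same formula at b = 20% gives about 48% if prevalent cases count and 62% for new onset (125 × 0.80 = 100 per arm).

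**Step 4, a second assumed pair.** With new onset of 35% versus 20%, 156 per arm and b = 20%, power is 58% if prevalent cases count and 76% for new onset.

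**Step 5, imbalance.** Let new onset be 25% in both arms, so that the fluid has no effect, and let prevalence be 25% in one arm and 15% in the other. The counted rates are 0.25 + 0.75 × 0.25 = 43.75% and 0.15 + 0.85 × 0.25 = 36.25%. The result is a spurious difference of 7.5 points.

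**The case against.** The strongest objection is that the article is silent, and silence is not a rule. Nowhere does it say that disturbances present at enrolment count. It is a condensed account, and cut-offs, time windows and baseline handling for a secondary laboratory outcome are often left to the full protocol or the analysis plan. This stands in part. A reader might infer that the outcome does count prevalent cases and that the chloride comparison is diluted. The text supports only the conditional statement: nothing printed keeps such cases out.

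Three further limits stand.
- A reader might infer that hyperchloremic patients with chloride up to 120 mmol/L are certain to be enrolled. That needs a cut-off of 120 mmol/L or lower, and none is given. With a higher cut-off nobody could have hyperchloremia at entry. The other five disturbances have no entry limit, so the point holds for them in any case.
- A reader might take the six states as one any-of-six composite. The article lists them without defining a composite, and the calculation above treats hyperchloremia alone.
- Making every prevalent case an event is the worst case. If the outcome used later values only, some cases could resolve, perhaps differently by fluid, and the (1 - b) factor would not apply exactly.

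It can also be said that the general methods include t tests and regression, so a continuous or adjusted comparison is not ruled out. That is true, but the method the article assigns to rates is unadjusted. The regression it describes takes up variables found significant in univariate analysis, which is not a planned adjustment for the enrolment value.

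**Conclusion.** The point holds in conditional form and is a worthwhile, inexpensive improvement to a secondary outcome. Followed as printed, the plan lets disturbances present at enrolment into an unadjusted comparison between fluids assigned by open-label calendar month. If they are counted, equal prevalence b shrinks the risk difference by (1 - b), and unequal prevalence biases it.

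The direction follows from the algebra; the size cannot be fixed from the article. The loss of 8 to 20 percentage points of power in the table (77% to 69% at b = 10%, 66% to 46% at b = 30%) rests wholly on the assumed incidence and prevalence and on counting every prevalent case. The article claims no power for this outcome, so no design figure is contradicted. The primary outcome, MAKE28, is unaffected.

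**What to change.** In the outcome definition, analyse each of the six disturbances separately as new onset after enrolment among patients free of that disturbance at enrolment, with its cut-off and time window stated. Report prevalent cases separately by arm, and adjust for the enrolment value. If all patients should stay in the comparison, so that worsening or failure to resolve is also seen, compare post-enrolment values adjusted for the enrolment value instead.

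The cost is a line or two of text. Enrolment chloride must already be available to apply the exclusion; sodium and potassium should be recorded at the same time. The downside of the new-onset version is a somewhat smaller denominator for each outcome, about 125 rather than 156 per arm if 20% are already affected. In every scenario shown, power was still higher than when prevalent cases were counted.
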